## Abstract

Exposure to airborne particulate matter (PM) may affect neurodevelopmental outcomes in children. The mechanisms underlying these relationships are not currently known. We aim to assess whether PM affects the developing brains of schoolchildren in Poland, a country characterized by high levels of PM pollution. Children aged from 10 to 13 years (*n* = 800) are recruited to participate in this case–control study. Cases (children with attention deficit hyperactivity disorder (ADHD)) are being recruited by field psychologists. Population-based controls are being sampled from schools. The study area comprises 18 towns in southern Poland characterized by wide-ranging levels of PM. Comprehensive psychological assessments are conducted to assess cognitive and social functioning. Participants undergo structural, diffusion-weighted, task, and resting-state magnetic resonance imaging (MRI). PM concentrations are estimated using land use regression models, incorporating information from air monitoring networks, dispersion models, and characteristics of roads and other land cover types. The estimated concentrations will be assigned to the prenatal and postnatal residential and preschool/school addresses of the study participants. We will assess whether long-term exposure to PM affects brain function, structure, and connectivity in healthy children and in those diagnosed with ADHD. This study will provide novel, in-depth understanding of the neurodevelopmental effects of PM pollution.

## 1. Introduction

Air pollution has received increased global public attention in recent years as presenting a major risk to human health [1]. According to the estimates of the World Health Organization (WHO), ambient air pollution accounts for 4.3 million deaths per year [2]. Exposure to outdoor particulate matter (PM) with an aerodynamic diameter <2.5 µm (PM_2.5_) is the fifth-ranking risk factor for mortality worldwide [3]. Epidemiological, pathophysiological, and animal model studies provide extensive evidence that short- and long-term exposure to particulate air pollution causes cardiovascular diseases [4,5], contributes to respiratory health deterioration and allergy development [6,7], and can lead to lung cancer [8,9]. Organic compounds and trace metals in PM may harm human health throughout the course of life, beginning in utero [10,11,12,13].

PM has been found incorporated within human brain tissue. Most likely, it enters via the olfactory and the gastrointestinal nerves, and is associated with abnormal protein aggregation in the brainstem [14,15]. In studies investigating the effects of PM using rodent models, inflammation, histopathological changes in the brain [16], and behavioural alterations [17,18] have been attributed to PM exposure. Two recent studies on mice and rats showed that astrocyte function and mitochondrial activity in the cortex were severely affected by PM; larger effects were observed for exposure to smaller particle sizes [19,20]. Some studies have shown that PM can affect the structure and the functioning of the human brain [21], but the results of this research are far from conclusive. For example, prenatal exposure to PM was negatively linked with cortical thickness in children aged between 6 and 10 years and was associated with impairment in inhibitory control [22]. Prenatal exposure to PM is also associated with decreased size of the corpus callosum and higher prevalence of behavioural problems in children aged between 8 and 12 years [23]. Postnatal air pollution exposure has been found to be associated with altered functional connectivity during rest [24]. Another study [17] has reported changes in grey matter surface area, volume, and thickness, but with no effect on cognitive functioning assessed by the comprehensive National Health Institute (NIH) Toolbox Cognitive Battery in children aged 9–10 years. Although exposure to PM has been reported to increase inattention, hyperactivity [12], and impulsivity symptoms [22]; lead to the lower intelligence quotient (IQ) [25]; and impact the prevalence of attention deficit hyperactivity disorder (ADHD) in children [26], the evidence for these effects is far from conclusive. In sum, the effects of PM and air pollution on neurodevelopment merit extensive further study.

Emissions of many air pollutants in the European Union (EU) have decreased over the past three decades, and air quality is gradually improving. In particular, between the years 2000 and 2014, significantly decreasing trends in annual average concentrations of PM with an aerodynamic diameter <10 µm (PM_10_) and nitrogen dioxide (NO_2_) were reported [27,28]. Despite these improvements, EU urban populations are exposed to PM levels that exceed the WHO limits for the protection of human health [29]. Between 2000 and 2010, the daily limit value for PM_2.5_ and PM_10_ concentrations in the EU were exceeded from 16 to 52% and from 18 to 44% of days, respectively [29]. These exceedances of PM limit values have mostly been observed in the eastern EU countries of Bulgaria, the Czech Republic, Slovakia, and Poland [28,29]. 

Most of the PM pollution in Poland results from the combustion of coal and other fossil fuels in power and heat generation, and from traffic emissions [30,31]. Estimates of the mortality attributable to PM_2.5_, based on air quality monitoring data for Poland, have demonstrated that the urban Polish population experiences an unduly high impact from particulate air pollution on their health [32]. Annual deaths attributable to air pollution in Poland were estimated at 39,800 for the year 2000, increasing to 47,300 deaths for the year 2017 [33]. 

The overall objective of the NeuroSmog study is to assess whether long-term exposure to outdoor PM affects brain function, structure, and connectivity in both healthy children and in those diagnosed with ADHD. Primarily, we will focus on the effect of PM on neural systems for attention and inhibitory control. In addition to neuroimaging, impacts of PM on these systems will be investigated using behavioural tests, including IQ. To meet the study aim, we assembled a multidisciplinary team of experts comprising air pollution modellers, environmental epidemiologists, neuroscientists, and clinical psychologists.

## 2. Methods

### 2.1. Study Area

We selected towns in southern Poland, based on their levels of particulate air pollution and population size, that are located within two hours’ drive to the magnetic resonance imaging (MRI) scanning centre in Kraków. The particulate air pollution level of each candidate town (*n* = 202) was classified as high, medium, or low based on the population-weighted median air pollution level inferred from 1 km × 1 km interpolated PM_2.5_ data for the year 2015 [34]. We chose small and large towns across different levels of air pollution to minimize urbanicity-related confounding. Towns with more than 90,000 inhabitants were classified as large; others were classified as small. Accordingly, we selected 18 towns (Table 1, Figure 1). 

We are recruiting comparable numbers of children (cases and controls) for each combination of air pollution level and town population size (Table 1). Within each such combination, the number of children recruited per town is approximately proportional to the town’s population size. 

### 2.2. Study Design and Study Population

Recruitment of study participants began in October 2020, with the aim of having 800 children complete all study procedures by the end of 2022. We are recruiting one ADHD case (intended number *n* = 267) per two population controls (intended number *n* = 533).

Cases with ADHD diagnosis according to the 11th revision of the International Classification of Diseases and Related Health Problems (ICD-11) [35] are recruited by field psychologists in the study towns. Children at risk of ADHD are referred to the psychologists either by cooperative school psychologists or teachers, or by paediatricians, psychologists, psychiatrists, or neurologists from psychological-educational counselling centres and mental health centres. In addition, cases are also recruited from families who voluntarily contacted us after seeing our recruitment advertisements.

We use a two-step model to verify and eliminate ADHD diagnosis in cases and controls, respectively (see Section 2.6). Firstly, a comprehensive psychological assessment is administered and evaluated by field psychologists. Secondly, three consultant clinical psychologists review the assessments to verify the diagnoses according to the ICD-11. Cases that do not meet the ICD-11 criteria are excluded from the study; controls who meet the ADHD diagnostic criteria are recruited into the case arm. 

All study participants are fluent Polish speakers, aged between 10 and 13 years, have average or above average intelligence (i.e., attend non-specialised schools), are in grades IV–VI, and attend school in the selected towns. Exclusion criteria for all are diagnosed intellectual disability, neurological or comorbid psychiatric disorders, other serious medical conditions, as well as contraindications to MRI. Children born before the 35th week or after the 40th week of gestation, or with birth weight <2500 g or with an Apgar score <8 are also excluded. As we are interested in the long-term effects of air pollution, children who resided outside of Poland during the last year are also excluded, as are children whose legal guardians are not fluent in Polish. 

A team of field psychologists with at least five years of clinical experience was recruited to enlist potential cases and perform psychological evaluation of all children. Prior to beginning their work, all psychologists received accredited training in the use of psychological tests utilised in the study (see Section 2.6). They were also trained in the administration of two behavioural tests (see Section 2.7), as well as in data protection and privacy laws.

Population controls are recruited from randomly selected larger non-specialized primary schools within each of the study towns (one to five schools per town). Lists of candidate schools were retrieved from the Boards of Education (Kuratoria Oświaty). Within each of the selected schools, classes are randomly selected in grades IV–VI. Within each class, one to five pupils are selected at random. The sampling is defined a priori using randomized lists defining which classes in every grade and which pupils in every selected class to approach and in what order. The randomization was implemented using the *sample.int()* function in R statistical software [36]. 

Headteachers of selected schools are contacted and asked to support the study’s recruitment campaign and sign a formal collaborative agreement. Participating schools are promoted on the project website, and are offered workshops on neurodevelopment and on the study results. Consent for contact from the legal guardians is obtained by the schools. Families who give their consent are contacted by telephone by research assistants. The assistants explain the study aims and procedures, confirm study eligibility, and invite the legal guardians to participate in the study. 

If a school does not agree to participate, the next school in the randomized list of schools is contacted. If the legal guardians of a selected child do not consent to being contacted, the next family from the randomized list of pupils is contacted. Where insufficient numbers of pupils are recruited in each grade, additional pupils are selected from the next class in the randomized list of classes (for that grade) using the same procedure until the desired number of pupils are recruited.

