## 4. Challenges

The COVID-19 pandemic, and disruptions to work, movement, and education that are associated with it, have greatly complicated the fieldwork component of the study. Even under normal conditions, the logistics of managing fieldwork across multiple centres are challenging. In general, all fieldwork has required more effort than originally anticipated and is taking longer than planned. The pandemic has also impacted negatively on response rates: 50% of contacted schools declined to collaborate and outreach towards the remaining 50% remains challenging.

Use of MRI in research presents additional challenges. Some members of the public distrust MRI and, on occasion, it has been difficult to motivate families of both cases and controls to participate in the study. A mixed attitude towards research involving underaged participants, exacerbated by the recent rise of anti-vaccine sentiment, also poses a challenge.

Although we will be able to assess lifelong exposure to air pollution in our study, we are only able to investigate the associations with a limited number of air pollutants. Our PM measures are gross, and we have no knowledge of its actual composition, which could vary considerably across Poland. There are a host of environmental stressors that could potentially affect neurodevelopment and be associated with air pollutants (and therefore cause confounding). The study would be better able to capture some of the wide array of environmental chemicals which might affect neurodevelopment if we had biological samples. Finally, as with all case–control studies, we anticipate that recall bias may affect our analyses, particularly in terms of early life factors and residences.

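### With ADHD diagnosis as outcome, cases and controls share no stated sampling frame, so the within-town PM odds ratio is open to selection bias of unknown direction

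*Protocol article*

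**What the plan says.** Section 2.2 sets the size and ratio of the groups: "We are recruiting one ADHD case (intended number *n* = 267) per two population controls (intended number *n* = 533".

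Controls enter through schools only: "Population controls are recruited from randomly selected larger non-specialized primary schools within each of the study towns (one to five schools per town". Classes and pupils are then drawn from randomised lists. Refusing schools are replaced: "If a school does not agree to participate, the next school in the randomized list of schools is contacted". Section 4 reports the refusal rate: "50% of contacted schools declined to collaborate and outreach towards the remaining 50% remains challenging".

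Cases enter by several routes. One is school staff: "Children at risk of ADHD are referred to the psychologists either by cooperative school psychologists or teachers". Others are paediatricians and specialists, including those at counselling and mental health centres. Section 2.2 adds a further route: "cases are also recruited from families who voluntarily contacted us after seeing our recruitment advertisements".

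The location rule common to both groups is attendance at a non-specialised school in a study town, in grades IV to VI. Section 2.1 balances recruitment by town pollution level and town size, with numbers per town roughly proportional to population. Section 2.9 assigns PM to home, preschool and school addresses. Table 4 lists ADHD diagnosis among the main outcomes, and section 2.10 includes ADHD in one of its seven outcome domains.

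**The concern.** In a case–control comparison, the controls should show the exposure distribution of the population from which the cases arose. Here the two groups pass through different filters below town level. Controls are filtered by school size and by the school's willingness to take part. Cases pass neither filter, and some select themselves.

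This matters because exposure is defined by place. If any of these filters is related to PM within a town, mean PM differs between cases and controls even when PM has no effect on ADHD. The balance described in section 2.1 works at the level of town type and does not reach differences between neighbourhoods. A null could then appear as a protective or a harmful association. Section 4 mentions school refusal as a response-rate problem and names recall bias, but does not mention the different sources of cases and controls.

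**Working it through.** **Step 1: the plan's own figures.** 800/3 = 266.7, rounded to 267 cases; 1600/3 = 533.3, rounded to 533 controls; 267 + 533 = 800. The stated split reproduces. The article gives no figure for PM differences between schools or neighbourhoods, so everything from step 4 on rests on assumed ranges.

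**Step 2: the two sources side by side.**
- School size: controls come from larger schools only; no limit is stated for cases.
- Number of schools: one to five per town for controls, so 18 × 1 = 18 to 18 × 5 = 90 in all; no limit is stated for cases.
- School consent: required for controls, with half of contacted schools declining; not stated as a condition for cases.
- Self-referral: described for cases only.
- Overlap: both groups meet the same eligibility rules, and controls found to meet ADHD criteria move to the case arm.

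**Step 3: which contrast carries the odds ratio.** Recruitment aims for comparable numbers in each combination of pollution level and town size, at 1:2 overall. If the 1:2 ratio also holds roughly by town, differences between towns say little about ADHD. The odds ratio then depends mainly on contrasts within towns, which is where the sources differ.

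**Step 4: illustration of the systematic part.** Let δ be the shift in mean control PM, in SD units, caused by selection alone. With roughly normal exposure of equal SD in both groups, the log odds ratio per SD under no true effect is about −δ. The standard error of the difference in means, treating all children as independent, is √(1/267 + 1/533) = 0.075. The chance of a nominally significant result at two-sided 5% is Φ(δ/0.075 − 1.96) + Φ(−δ/0.075 − 1.96).
- δ = 0.05: OR about 0.95 (1.05 if control areas are the cleaner ones); about 10% significant.
- δ = 0.10: OR about 0.90 (1.11); about 27%.
- δ = 0.20: OR about 0.82 (1.22); about 76%.

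**Step 5: the random part, kept separate.** With m controls per school and intra-school correlation ρ of PM (assumed), the design effect is 1 + (m − 1)ρ, and the standard error becomes √(1/267 + design effect/533). Cases are treated as unclustered.
- 18 schools, m = 533/18 = 29.6. At ρ = 0.05, 0.2, 0.5 the design effect is 2.43, 6.72, 15.31; effective controls 219, 79, 35; standard error 0.091, 0.128, 0.180.
- 90 schools, m = 533/90 = 5.9. At the same ρ the design effect is 1.25, 1.98, 3.46; effective controls 428, 269, 154; standard error 0.078, 0.086, 0.101.

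The schools are drawn at random, so this part widens the honest interval but leaves the expected difference at zero.

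**The case against.** The strongest reply is that the sources are closer than they look. Both groups must attend non-specialised schools in the same towns, school staff refer cases, and screen-positive controls become cases. What counts as a larger school is not defined, so these schools may hold most pupils. The exposures of interest also include prenatal, early-life and lifetime PM built from full address histories, and the present school ties down earlier addresses only loosely. Nothing in the article shows that larger or consenting schools lie in more or less polluted areas. Section 1 places the primary focus on neural systems for attention and inhibition, not on ADHD as an outcome.

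Most of this stands, and it limits the point. The overlap and the address histories would shrink any shift, most of all for prenatal exposure. They do not remove it: no common school frame is stated, school addresses enter the exposure directly, and ADHD diagnosis remains a listed main outcome.

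A further reply is that school clustering belongs in a statistical analysis plan. That is right. The article says only that regression will be used, so step 5 shows why clustering is needed and does not show that it was left out.

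**Conclusion.** The point holds for analyses with ADHD diagnosis as outcome. The stated design gives cases and controls different filters below town level, and any filter related to PM biases the within-town odds ratio. Direction and size are unknown. The range of 0.95 to 0.82, or its inverse, follows from assumed shifts of 0.05 to 0.2 SD and is not an estimate of what will happen. Analyses of brain or cognitive outcomes within one group are much less affected.

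A reader might infer more, and the documents do not support it:
- That the draw of a few schools is itself a source of bias. The draw is random and adds clustered error only.
- That false-positive rates will be inflated by a known amount. That needs an analysis ignoring school, which the article does not state, and an intra-school correlation that it does not give.
- That families answering advertisements were selected on concern about smog. The advertisement text is not shown.
- That the sign of a true effect will be reversed. The illustration covers only the case of no effect.
- That the study's main result is at stake. ADHD falls within one of seven outcome domains.

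**What to change.** For the ADHD-diagnosis analysis:

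1. Pre-specify a common-frame analysis restricted to cases whose school is on the candidate list of larger schools used for controls, reported beside the full-sample result. The candidate lists exist (section 2.2), and school addresses are collected by the Address Questionnaire (section 2.5). This deals with the school-size filter, but not fully with school refusal.
2. Use variance clustered on school.
3. Record route of entry from now on, since the article does not say that it is stored, and repeat the analysis without advert-recruited families. At the time of writing 370 children had been evaluated, so 800 − 370 = 430 of the target were still to come; for those already seen, the route would have to be recovered from existing records where possible.
4. Name the differing case and control sources as a limitation in section 4.

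Adjustment for residential density should be left out unless the causal diagram supports it: residential area is itself a predictor in the PM model (Table 3), and section 2.10 aims to avoid overadjustment.

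The cost is one added recruitment field, some analysis text, and fewer cases with wider intervals in the restricted analysis. No new assessment of any child is needed.

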### 2.3. Study Timeline Overview and Progress

All psychological and behavioural assessments are performed during three meetings with the field psychologist. Each meeting lasts about one hour and twenty minutes to two hours, and both the child and their legal guardian are present. At the final meeting, the results of the assessments are explained to the child and to their guardian, a formal psychological evaluation is provided. The MRI scan is completed in Kraków within three months of the psychological evaluation. Typical MRI sessions last up to one and a half hours. After the MRI session, families are rewarded with vouchers equal to 270 PLN (about 60 EUR at the time of writing) and are reimbursed for travel expenses. The children receive t-shirts printed with MRI images of their brains. 

Figure 2 illustrates the progress in the recruitment of controls at the end of the first study year (June 2021). 

A total of 370 children have undergone psychological evaluation, of whom 236 have also completed the MRI scan. Figure 3 depicts the number of cases and controls tested in each town at the end of August 2021.

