### 2.4. Data Management

Behavioural testing is conducted on HP laptops with 15.6” screens, set up identically for each field psychologist. The laptops are encrypted using BitLocker and synchronised with a secure OneDrive cloud folder at the Jagiellonian University that collects raw data from every test performed. 

To minimise the impact of the study on the environment and to reduce transcription from paper to computer, the psychological data are—wherever possible—collected digitally using online questionnaires implemented in survey tools developed by Qualtrics (https://www.qualtrics.com, accessed on 23 December 2021). 

The raw data are processed and prepared for import in R and Python. To allow easy data selection and extraction of variables of interest by data analysts, a secure user website will be implemented that will interface with an SQLite database.

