**Psychological evaluation**	
CBCL and YSR	Total problems
	Internalizing problems
	Externalizing problems
	Withdrawn/depressed
	Somatic complaints
	Anxious/depressed
	Social problems
	Thought problems
	Attention problems
	Rule-breaking behaviour
	Aggressive behaviour
SB5	General IQ
	Verbal IQ
	Non-verbal IQ
PU1	Selective attention
	Memory–phonological loop
	Visual–spatial memory
	Executive functions
Opinions of assessing psychologists, Conners 3, PU1, SB5, CBCL, and validation	ADHD diagnosis

ADHD—Attention deficit hyperactivity disorder; ANT—attention network test; BOLD—Blood oxygen level dependent effect; CARIT—Conditioned approach response inhibition task; CBCL—Child Behaviour Checklist; CPT—Continuous performance test; DWI—CDiffusion-weighted imaging; fMRI—Functional magnetic resonance imaging; IQ—Intelligence quotient; MP2RAGE—Magnetization-prepared 2 rapid acquisition gradient echo; NODDI—Neurite orientation dispersion and density; PU1—Bateria diagnozy funkcji poznawczych PU1: Pamięć—uwaga—funkcje wykonawcze (Diagnostic Battery for Cognitive Functions Evaluation); SB5—Stanford-Binet Intelligence Scales, 5th edition; T1-w—T1-weighted; T2-w—T2-weighted; YSR—Youth Self-Report.

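### SB5 and PU1 scores come from a team of field psychologists in towns chosen for PM contrast, and the regressions named in 2.10 include no examiner term

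*Protocol article*

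**What the plan says.** **Who tests.** Section 2.3 of the protocol article: "All psychological and behavioural assessments are performed during three meetings with the field psychologist". Section 2.2 describes a team "recruited to enlist potential cases and perform psychological evaluation of all children", and says that cases "are recruited by field psychologists in the study towns". The natural reading is one examiner per child and several examiners in the study. The size of the team and its allocation to towns are not given.

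**Where.** Section 2.1 selects 18 towns by PM level and population size. Section 2.9 assigns exposure by residential and school address, so some PM variation lies within towns.

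**What depends on the examiner.** Table 4 lists SB5 and PU1 scores among the main outcomes. It also lists ADHD diagnosis, based on "Opinions of assessing psychologists, Conners 3, PU1, SB5, CBCL, and validation".

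**Safeguards.** Section 2.2 requires at least five years of clinical experience and accredited test training. Laptops are "set up identically for each field psychologist" (2.4), and children practise the computer tasks to 90% accuracy (2.7). For diagnosis there is a second step: "three consultant clinical psychologists review the assessments to verify the diagnoses according to the ICD-11". No second scoring of SB5 or PU1 is described.

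**Analysis.** Section 2.10 plans a separate regression for each exposure-outcome pair, with confounder sets chosen by DAG. It names no examiner term.

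**The concern.** For SB5 and PU1 the examiner is part of the measuring instrument. Prompting, pacing and scoring differ somewhat between trained examiners, and these differences are shared by every child whom one examiner sees. If an examiner's children come mostly from towns of one PM level, the shared difference enters the PM contrast. Ordinary regression then treats those children as independent and reports a standard error that is too small.

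The article takes this threat seriously for MRI: section 3 gives the single scanner as protection against acquisition differences. For the psychologist-administered tests there are several examiners, and nothing described measures or adjusts for what remains after training.

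The stated rule for choosing covariates may not catch it. An examiner does not cause PM exposure, so a DAG of ordinary confounders can leave examiner out unless town and outcome measurement are drawn in. At stake are the error rates and intervals of the IQ and cognitive papers.

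**Working it through.** The article gives no power figure, number of examiners or examiner variance, so there is no figure of its own to reproduce.

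**Inputs from the article.** 800 children (2.2). Comparable numbers in each of the six PM-by-size combinations (2.1), taken as equal: 800/6 = 133.3 per combination and 800/3 = 266.7 per PM level. Table 1 has 6 + 8 + 4 = 18 towns.

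**Assumptions, not in the article.** Scores in SD units; examiner SD s = 0.1 to 0.3; k = 3 or 6 examiners per PM level, with equal loads, each confined to one level; high level compared with low.

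**Step 1, SE that ignores examiners.** sqrt(2/266.7) = 0.087.

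**Step 2, true SE under nesting.** sqrt(0.087² + 2s²/k).

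**Step 3, actual error of a nominal 5% test.** 2 × [1 − Φ(1.96 × 0.087/true SE)].

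| k per level | s | True SE | Actual error |
|---|---|---|---|
| 3 | 0.1 | sqrt(0.0075 + 0.0067) = 0.119 | 15% |
| 3 | 0.3 | sqrt(0.0075 + 0.0600) = 0.260 | 51% |
| 6 | 0.1 | sqrt(0.0075 + 0.0033) = 0.104 | 10% |
| 6 | 0.3 | sqrt(0.0075 + 0.0300) = 0.194 | 38% |

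**Step 4, the opposite allocation.** If every examiner tests equally at both levels, examiner effects cancel from the contrast and there is no inflation. Left out of the model, they stay in the residual and enlarge the reported SE by a factor sqrt(1 + s²): sqrt(1.01) = 1.005 to sqrt(1.09) = 1.044. The lost precision is about 0.5% to 4%.

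**Step 5, check on a layout closer to the study.** A null simulation used about 800 children in the 18 towns, IQ SD 15 and 1,500 runs per setting. It assumed that 20% of PM variance lies within towns and that examiners account for 2%, 5% or 10% of score variance. Examiners covered one town each (18), or blocks of towns adjacent in PM level (9 or 6), which is unfavourable. Rejection rates of ordinary regression at nominal 5%:

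| Examiners | 2% | 5% | 10% |
|---|---|---|---|
| 18 | 0.20 | 0.35 | 0.46 |
| 9 | 0.28 | 0.42 | 0.54 |
| 6 | 0.26 | 0.43 | 0.56 |

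The mean slope stayed near zero (−0.04 to 0.07 IQ points per SD of PM). Its SD across studies was 0.80 to 1.81, against a reported SE of about 0.53. So there is no systematic bias when examiner differences are unrelated to PM. The harm is false precision and a chance shift in the one study that is run. Standard errors clustered on examiner brought the rates down to 0.12 to 0.17, not to 0.05, because the clusters are few and unequal.

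**The case against.** The best reply is that the premise is undocumented. Working in the study towns describes the team and ties no psychologist to a town or PM level, and the singular in section 2.3 may be generic. This stands: alignment is a possibility to be checked.

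A second reply is that a condensed article leaves covariates and error structure to an analysis plan that is not shown. That also stands in part. The absence of a named examiner term is not in itself an error, and a DAG that includes town and measurement could lead to one. What remains is that the one covariate rule given is aimed at confounders and can pass over the examiner.

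Third, experience, training and identical equipment shrink examiner differences. They do, but by an unmeasured amount.

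A reader might also infer three stronger claims that the article does not support:

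- *A lenient examiner would create a PM effect on ADHD frequency.* Recruitment aims at comparable numbers of cases and controls in each PM-by-size combination, at one case per two controls, so the case share by PM level is largely set by quota. Consultants also verify diagnoses.
- *Clustering on town would fail.* No town clustering is planned, so there is nothing to rebut.
- *Remaining children should be reassigned among psychologists.* With three meetings per child this is not clearly cheap, and no documented misallocation calls for it.

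**Conclusion.** The point holds in limited form and is worth acting on, mainly because the remedy is nearly free. It concerns SB5 and PU1. The computer tasks and the guardian- and child-completed scales are less exposed, and the MRI outcomes, which are the study's primary focus, come from one scanner.

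The size is uncertain. The 15% to 51% range is a worst case that rests on an assumed examiner SD, three examiners per level and complete nesting of examiners in PM level. Inflation is close to zero under full crossing. The article does not show where between these the study lies. Confidence that a material distortion is present is low. Confidence that an examiner term and an allocation table are sensible is considerably higher, since they give more honest intervals under nesting and slightly tighter ones under crossing.

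**What to change.** 1. Keep examiner ID in the analysis dataset. Laptops are set up per psychologist, so identity should be recoverable, but the article does not say that it is stored; confirm this.
2. Include examiner as a random effect in every SB5 and PU1 model, alongside town where the two can be separated. Use small-sample degrees of freedom if examiners are few. Fit the same term for the laptop tasks as a sensitivity analysis.
3. Report the table of examiner by PM level. It shows directly whether the problem exists.
4. Where examiners span PM levels, add the within-examiner PM slope (examiner as a fixed effect) as a sensitivity analysis.
5. Where examiner and town coincide, say that they cannot be separated, and rely on within-town PM contrasts from the address-level exposure. A random effect widens the interval in that case but cannot take a realised examiner shift out of the estimate between towns.

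**Cost.** One model term, one table and one sensitivity analysis, with no change to fieldwork. The downside is wider confidence intervals if examiners turn out to be nested in PM level.
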